**Participant satisfaction**				
	1. Investigator-generated program evaluation measures [62].	—	—	X
	2. Qualitative, open-ended user evaluation questions.	—	—	X
**Built and social environment**				
	1. Office Spatial Layout: Employees rate office environment features (eg, office layout and coworker proximity) on a 5-point scale; test-retest intraclass correlation coefficient=0.70-0.87, associated with occupational sitting (*P*<.05) [63].	X	—	—
	2. Employees rate reactions of coworkers, supervisor, family members, and friends to their elliptical use on a 5-point investigator-generated scale.	—	—	X

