## Methods

### Design

We will use a 2 (gift card type: healthier food vs Amazon) by 3 (gift card schedule: immediate incentive contingent on individual pedaling quantity, immediate incentive partially contingent on dyads’ joint pedaling quantity, and delayed noncontingent pedaling incentive) cluster randomized within-subjects factorial design. Employee dyads (n=60 or 30 two-person clusters) will be recruited on a rolling basis to join the program together and will be randomly assigned in clusters to 1 of the 6 study groups using computer-generated permuted block randomization (block size of 6 with equal allocation, determined by a statistician).

The intervention phase will last 4 weeks, with within-subject assessments (via pre- and postintervention questionnaires) used to capture changes in work performance and reported nonpedaling physical activity between a 4-week preintervention period with standard office sitting and a 4-week intervention period with desk pedaling. The primary outcomes are (1) changes in employee- and supervisor-reported work performance between the 4-week preintervention period and the 4-week intervention period and (2) objectively measured pedaling quantity during the 4-week intervention period based on data from the Bluetooth-enabled desk ellipticals. The secondary outcomes include employee-reported changes in nonpedaling physical activity, cost-effectiveness of incentive conditions (measured by the total dollar value of gift cards distributed and redeemed, and by work productivity and body weight changes), participant satisfaction, and built and social environment influences on employees’ work performance and pedaling quantity.

The study was approved by the Pennsylvania State University College of Medicine Institutional Review Board, and the National Institutes of Health peer-review statements are included in Multimedia Appendices 1 and 2.

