**Demographic and health characteristics**				
	1. Employee demographics, self-rated health, height, and weight.	X	—	X
	2. Supervisor demographics.	X	—	—

^a^M0=preintervention.

^b^M1=4-week intervention phase.

^c^M2=postintervention.

^d^The symbol “X” indicates that a measure was administered at this assessment point.

^e^A measure was not administered at this assessment point.

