#### Effects of Incentive Condition on Desk Pedaling Quantity

For the study’s second goal, to assess the effects of the 6 incentive conditions on pedaling quantity (miles and minutes) completed over 4 weeks, we will model elliptical miles and minutes per day as continuous outcomes using linear mixed effects models with repeated observations of each outcome variable (level 1) treated as nested within (n=60) individual participants (level 2), while accounting for clustering effects within each dyad (level 3). We will add to our models effect coded vectors for gift card type (food vs Amazon) and gift card schedule (Usual Delayed Reward vs ICIR vs JCIR) to test for main effects; along with gift card type×gift card schedule interaction terms to test for simple effects across cells.

Covariates will be included in all analyses to adjust for participants’ demographic and health characteristics (eg, age, gender, race and ethnicity, education, body mass index, and nonpedaling physical activity). Finally, we will use multivariable mixed effects models to explore the association of employees’ demographic and health characteristics, social and built-office environment factors, and supervisor characteristics with employees’ work performance and pedaling quantity. All mixed effects models will follow an intention-to-treat principle, using all available data.

Other secondary analyses will depend on the specific research question and the most appropriate statistical or qualitative methods for the design.

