### Comparison With Prior Work

Previous research indicates that employees can pedal desk pedaling devices without detrimental effects on objectively measured nonpedaling physical activity [30,76] and employee-rated work performance [13,29,30], and that there is interest in using these devices among adults with multiple health risk factors [77]. Our study adds to this early literature by including measures important for guiding wider dissemination of desk pedaling devices, including supervisor ratings of employee work performance, the differential effects of different incentive strategies on pedaling volume, social and built-office environment influences on desk pedaling, and qualitative assessment of user-encountered issues. Our study also allows enrollment of participants with greater health risks than most previous similar studies, which can inform the real-world generalizability of desk pedaling.

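### Reactions to elliptical use are rated only after the pedaling is complete, so they should not be modeled beside baseline predictors or reported as a social influence

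*Protocol article*

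**What the plan says.** The Design section of the protocol article lists among the secondary outcomes "built and social environment influences on employees’ work performance and pedaling quantity". In the Discussion, under Comparison With Prior Work, "social and built-office environment influences on desk pedaling" appears among the measures the study adds to guide wider dissemination.

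The Built and social environment block of Table 1 has two items:

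- Office Spatial Layout: "Employees rate office environment features (eg, office layout and coworker proximity) on a 5-point scale". It is marked at M0 only.
- Reactions of others: "Employees rate reactions of coworkers, supervisor, family members, and friends to their elliptical use on a 5-point investigator-generated scale". It is marked at M2 only, and the footnote gives "M2=postintervention".

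The pedaling outcome is "objectively measured pedaling quantity during the 4-week intervention period", that is, M1. Employee and supervisor performance ratings are taken at M0 and M2; the employee rating of performance by task type is taken at M2 only.

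The last part of the Statistical Analysis section (Effects of Incentive Condition on Desk Pedaling Quantity) plans multivariable mixed models that relate demographic and health characteristics, "social and built-office environment factors, and supervisor characteristics" to work performance and pedaling quantity. It describes these models as exploring associations. It does not name the reactions item, but that item is the only rating of other people's responses in the corresponding block of Table 1, so the natural reading is that it enters as a social factor.

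**The concern.** The reactions item asks about responses to the employee's own elliptical use. Someone who pedals a lot gives others more to respond to, and someone who hardly pedals has little to rate. The score may therefore follow from pedaling as easily as it leads to it, and it is recorded when pedaling can no longer change. For employee-rated performance, the same person gives both ratings at the same assessment, so an employee who feels the month went well may rate both more favorably.

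Two things are at stake. First, the coefficient for reactions has no identifiable direction, while the outcome list and the Discussion word the result directionally. Second, a variable that may be a consequence of the outcome would sit beside predictors measured at M0 in one model, and can shift their coefficients. The M0 factors are the part of this secondary question that does have time order, so the second effect could spoil the more usable result.

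**Working it through.** The plan gives no figure on this point, so there is none to reproduce. The check is of timing, then of what the model can recover.

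**1. Order of measurement (Table 1)**

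| Variable | M0 | M1 | M2 |
|---|---|---|---|
| Office layout, coworker proximity | X | | |
| Pedaling (device) | | X | |
| Reactions of others | | | X |
| Employee-rated overall performance | X | | X |
| Supervisor-rated performance | X | | X |

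Office layout precedes both the pedaling and the post-period ratings. Reactions follow all the pedaling and are taken at the same assessment point as the post-period performance ratings. No repeated or mid-intervention reactions rating is scheduled.

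**2. Can one post-period score show direction?** An illustrative simulation used 60 participants in 30 dyads, the plan's intracluster correlation of 0.05, 20 workdays (5 × 4 weeks) and 4,000 runs. Each participant's mean pedaling was regressed on one reactions score by ordinary least squares, a simplification of the planned mixed model. The true correlation of 0.4 is an assumption.

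| How the data arose | Mean slope | SD over runs |
|---|---|---|
| Reactions drive pedaling | 0.399 | 0.125 |
| Pedaling drives reactions | 0.401 | 0.127 |
| Common cause of both | 0.399 | 0.123 |

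The agreement is what theory predicts: the three mechanisms give essentially the same joint distribution of the two variables. Another assumed correlation would change the slope but would not reveal the direction.

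**3. What happens to an M0 predictor in the same model?** Let X be an M0 factor, Y pedaling and R reactions, all standardized. In the regression of Y on X and R, the coefficient of X is

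(r_XY − r_XR × r_RY) / (1 − r_XR²).

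*Case A: R depends on Y only.* Put r_XY = b and r_RY = c, so r_XR = bc. The coefficient becomes b(1 − c²)/(1 − b²c²), although the total association of X with Y is b. With b = 0.3 assumed:

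- c = 0.3: ratio to b = 0.91/0.9919 = 0.917
- c = 0.4: 0.84/0.9856 = 0.852
- c = 0.5: 0.75/0.9775 = 0.767

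So the M0 coefficient shrinks by about 8%, 15% and 23%.

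*Case B: X has no relation to pedaling but does affect reactions* (nearby coworkers, for example, may comment more). Then r_XY = 0, and with r_XR = a the coefficient is −ac/(1 − a²). With a = c = 0.3 assumed, this is −0.09/0.91 = −0.099: a negative association produced only by the adjustment.

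The correlations in step 3 are assumptions that show the mechanism. They are not estimates for this trial.

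**The case against.** The strongest reply is that the analysis text is already modest: it says the models explore associations. It does not describe them as causal, and no sentence commits the investigators to reading a coefficient causally. That stands. A reader might infer from the Design and Discussion wording that the plan will present reactions as a proven lever for dissemination, but the document does not say so. What remains is a mismatch between the outcome wording and the analysis wording, plus the model-composition problem, which softer wording does not remove.

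A reader might also conclude that the whole social-environment question is unanswerable. That goes too far. Coworker proximity is measured at M0, open-ended evaluation questions are collected, and the randomized contrast between joint and individual contingency bears on one social factor, though the plan states that it is not powered for differences between incentive conditions. Only the reactions item is affected.

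Shared-rater bias should not be extended to every outcome either. Pedaling is recorded by the device, and supervisors give their own performance ratings. For those outcomes the problem is direction and common causes, not a shared rater.

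Finally, reactions to elliptical use could not be rated before installation, and one retrospective rating is a low-burden choice. That is fair. It explains the schedule but does not give the item the time order of an M0 predictor.

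**Conclusion.** The point holds for the reactions item alone. With one rating after the pedaling, neither the planned models nor any later analysis of that score can separate influence from consequence or common cause. This rests on the Table 1 schedule and needs no assumed correlation. That an M0 coefficient can be distorted follows from the regression formula; how much depends on unknown correlations, and the 8% to 23% above illustrates one assumed case. The point also rests on reading the planned social factors as including the reactions item.

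A high chance of a significant coefficient would not be evidence of error here. If reactions and pedaling really are correlated, finding that association is a correct result under a plan that speaks of association. The fault lies in the directional label and in the place of the item in the model.

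The analysis is secondary and exploratory, and neither primary aim is affected. The correction is still worth making because it changes the multivariable coefficients and what may be concluded from them.

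**What to change.** Before the 2020 analyses:

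- Leave the M2 reactions item out of the multivariable predictor models of pedaling and work performance.
- Report its relation to each outcome separately, as a descriptive association with no direction claimed. For employee-rated performance, including the task-type ratings, note that the same person gave both ratings.
- In the Design section and in Comparison With Prior Work, limit influence wording in these observational analyses to factors measured at M0, such as office layout and coworker proximity. These are still open to confounding, but they do precede the outcomes.

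This takes a change to the model specification and some rewording, with no new data. The price is that there will be no adjusted estimate for reactions and that the secondary claim becomes narrower.

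An optional addition for participants still to start is to ask the same items at the end of week 1 and relate them to pedaling in weeks 2 to 4, adjusted for week-1 pedaling. This would reduce the problem without removing it, because a week-1 rating still follows week-1 pedaling and can share stable causes with later pedaling. It adds a prompt during a 4-week behavioral intervention. With data collection due to end by December 2019, it would reach an unknown remainder of at most 60 participants, so the main fix should not depend on it.

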**Demographic and health characteristics**				
	1. Employee demographics, self-rated health, height, and weight.	X	—	X
	2. Supervisor demographics.	X	—	—

^a^M0=preintervention.

^b^M1=4-week intervention phase.

^c^M2=postintervention.

^d^The symbol “X” indicates that a measure was administered at this assessment point.

^e^A measure was not administered at this assessment point.

### Statistical Analysis

We will perform descriptive analyses for all measured variables. We will examine data normality and skewness, along with missing data and address any identified issues using standard procedures [27].

#### Effects of Desk Pedaling on Work Performance

For the study’s first goal, to test whether mean work performance scores during the 4-week desk pedaling intervention period are equivalent to performance during the 4-week preintervention period with standard office sitting, we will apply the equivalence test of means based on 2 one-sided *t* tests [64,65] with the significance level adjusted for multiple comparisons via the Bonferroni correction factor. We will also use the confidence interval approach for testing equivalence when regression models are considered [66].

We define equivalence based on 2 related standards: (1) the International Organization of Standardization ergonomic standard for computer keyboards indicates that average typing speeds obtained using a new keyboard must not exceed 0.75 standard deviations of average speeds for standard keyboards (in the direction of poorer performance) to be acceptable [67]; (2) in clinical research, a change of 0.50 standard deviations in health status sometimes is used as a basis for treatment modifications [68,69]. Using the approximate midpoint of these 2 standards, we define equivalence, or feasibility, for the desk elliptical as average work performance scores that do not exceed 0.60 standard deviations (in the direction of poorer performance) of average work performance scores obtained during standard office sitting.

We will also explore how work performance varies by tertiles of elliptical pedaling quantity. To evaluate changes in overall work performance, and work performance by task type, which are repeatedly measured, we will plot mean scores over time and conduct longitudinal analysis based on mixed effects models [70]. We will use random effects to account for measurement correlation within the same subject and clustering effects. The estimated time effect from mixed effects models will indicate whether performance increased, decreased, or remained stable over the preintervention and intervention periods.

For the qualitative assessment of participants’ capacity to pedal and work simultaneously, NVivo software (QSR International) will be used to organize data from the qualitative open-ended questions. A codebook will be developed to classify major themes, and data will be coded by 2 independent coders. Coding discrepancies will be discussed and resolved, and interrater reliability will be calculated.

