### Setting and Recruitment

The study is based at the Penn State Hershey Medical Center, a major teaching and research hospital with more than 12,000 employees in Central Pennsylvania [50]. Sedentary desk jobs at the medical center are diverse and include secretarial and administrative work, grant proposal preparation, budgetary administration, radiology and scan analysis, quality control initiatives, and faculty member and other research or clinical support positions. A brief study description was distributed via electronic newsletter to all employees to publicize the study. The study description contained a link to the secure REDCap site [51] to complete a screening form to assess inclusion and exclusion criteria. The study description was additionally emailed to administrative staff who were given the option of forwarding this information to department employees. Study information was also posted on Penn State’s research recruitment website. 

Employees who remain eligible to participate after completing the screening form are asked to provide their supervisor’s contact information. Supervisors then receive a brief study summary, together with a link to a secure Web-based REDCap form to enable them to document consent for their employee(s) to participate. Following receipt of the supervisor’s permission form, an initial study meeting is scheduled at the participant’s office. At this approximately 20-min meeting, the consent form and baseline questionnaire are administered, and the research team evaluates the participant’s desk setup to determine if modifications are required to ergonomically place the elliptical under the participant’s desk (eg, accessible electrical outlet to plug in the elliptical and relocation of underdesk items).

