#### Power and Sample Size

We assume that an equivalence margin standardized by the standard deviation is 0.60 for the primary outcome, based on clinical and industrial engineering standards [67-69]. We also assume an intracluster correlation of 0.05 and a significance level of 0.05. Therefore, a sample size of 50 (25 dyads) gives 80% power to detect equivalence when assessing the mean delta change in total work performance scores from the preintervention period to the intervention period. Anticipating 10% to 20% attrition, we expect to recruit up to 60 participants. The study was not powered to detect differences in pedaling volume by the 6 incentive conditions because of resource constraints and because a key exploratory goal was to assess feasibility and preliminary effects of different incentive strategies.

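### The equivalence test named for work performance carries no dyad adjustment, although the sample size assumes within-dyad correlation, and the cluster-aware route in the same section is not made decisive

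*Protocol article*

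**What the plan says.** All references are to the protocol article.

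- *Effects of Desk Pedaling on Work Performance*: for the first goal, "we will apply the equivalence test of means based on 2 one-sided" *t* tests, "with the significance level adjusted for multiple comparisons via the Bonferroni correction factor". The sentence names no dyad or cluster term and does not say whether the tests are paired.
- Same section, next sentence: "We will also use the confidence interval approach for testing equivalence when regression models are considered". This is added to the t tests and is not said to replace them.
- Same section, on the longitudinal analysis of work performance: "We will use random effects to account for measurement correlation within the same subject and clustering effects". The stated use of these models is to show whether performance rose, fell or stayed stable.
- *Power and Sample Size*: "We assume that an equivalence margin standardized by the standard deviation is 0.60 for the primary outcome"; "We also assume an intracluster correlation of 0.05 and a significance level of 0.05"; "a sample size of 50 (25 dyads) gives 80% power to detect equivalence".
- *Design* and *Inclusion and Exclusion Criteria*: participants enrol as two-person clusters of coworkers. A common supervisor is not required.
- *Setting and Recruitment*: supervisors receive a form "to enable them to document consent for their employee(s) to participate". The optional plural allows that one supervisor has more than one participant, but does not say so.

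**The concern.** The sample size treats partners' changes as correlated, and the test named for the same comparison has no term for that correlation. When partners' changes are positively correlated, a paired t test on individual participants understates the standard error of the mean change.

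In a superiority test that favours finding a difference. In an equivalence test it favours declaring equivalence, which is the result the authors hypothesise and the one employers would rely on. A false declaration here means assuring an employer that pedaling does not harm work performance when the decline has in fact reached the margin.

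A cluster-aware route is also planned and no order of precedence is given. The two routes can disagree near the margin, and the article does not say which answer would stand.

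**Working it through.** **Inputs.** From *Power and Sample Size*: margin 0.60 SD, ICC 0.05, alpha 0.05, N = 50 (25 dyads), power 80%. From *Design*: cluster size 2. The article does not give the true difference or the SD of change. Assumed here: true difference 0, and variance of change 2·SD² (pre–post correlation r = 0), because these values reproduce the stated N.

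**Step 1. Reproduce the stated sample size** (two one-sided tests, normal approximation).

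- Without clustering: N = 2·((z0.95 + z0.90)/0.60)² = 2·((1.645 + 1.282)/0.60)² = 47.58
- Design effect: 1 + (2 − 1)·0.05 = 1.05
- With clustering: 47.58 × 1.05 = 49.96, so 50. Power at N = 50 is 0.800.

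The stated N therefore includes the dyad design effect. It uses alpha 0.05 for each one-sided test, with no Bonferroni division.

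**Step 2. Error rate of a paired t test that leaves out the dyads.** At the margin, the error is governed by the one-sided test on that side. For clusters of two the true standard error is √(1 + ICC) times the one used, so

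false-equivalence rate = 1 − Φ(z(1−α)/√(1 + ICC)).

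At ICC 0.05, √1.05 = 1.025 and 1.645/1.025 = 1.605, giving 0.054.

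| ICC of change | Source | Nominal 5% | Nominal 1.25% (four comparisons assumed) |
|---|---|---|---|
| 0.05 | stated | 5.4% | 1.44% |
| 0.1 | assumed | 5.8% | 1.63% |
| 0.2 | assumed | 6.7% | 2.0% |
| 0.5 | assumed | 9.0% | 3.4% |

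Simulating the paired test at ICC 0.05 and nominal 5% (400,000 runs per setting) gave 5.4% with 25 dyads and 5.5% with 30.

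**Step 3. Dependence on pairing.** If the tests were unpaired, the rate at ICC 0.05 would be 1 − Φ(1.645/√((1 − r)·1.05)). That is 5.4% at r = 0, 2.8% at r = 0.3 and 1.2% at r = 0.5. The excess at positive r therefore requires the paired form.

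**Step 4. A cluster-respecting alternative.** A t test on dyad-mean changes (24 degrees of freedom with 25 dyads) had a simulated false-equivalence rate of 5.0% at every ICC tried from 0 to 0.5. Its power at ICC 0.05 and alpha 0.05:

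| | N = 50 | N = 60 |
|---|---|---|
| Margin as in step 1 (r = 0) | 0.77 | 0.86 |
| Margin in units of the SD of change | 0.98 | 0.99 |

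**Step 5. Shared supervisors (assumption only).** If one supervisor rated four participants, the design effect would be 1 + 3·ICC. The rate at nominal 5% would then be 6.3% at ICC 0.05 and 9.7% at ICC 0.2. The article gives neither the number of employees per supervisor nor an ICC for supervisor ratings.

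**The case against.** The strongest reply is that clustering was not overlooked. It is in the sample size, the mixed models carry random effects for it, and a confidence-interval route to equivalence stands directly after the t tests. *Design* defines the first primary outcome as change in work performance, so those models address the primary outcome itself. The statement in *Effects of Incentive Condition on Desk Pedaling Quantity* that covariates enter all analyses also points towards regression. A condensed article may leave the precedence of routes to an analysis plan that is not shown. The excess at the stated ICC is only 0.4 percentage points.

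Most of this stands. A reader might infer that the plan ignores clustering altogether; the text does not support that. A reader might also infer that the true error is in the range of 7% to 10%. Such figures need ICCs of about 0.3 or more at an unadjusted 5% level. The article states 0.05 and applies Bonferroni, and the relevant correlation is that of *change*, from which stable team or rater differences cancel. Nor does the article say that partners share a supervisor.

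Two things remain. First, the article does not leave the test open: it names one for the first goal, and as worded that test does not match the design effect behind the sample size. Second, the unpaired escape is unlikely. *Design* describes within-subject assessment and *Power and Sample Size* refers to the mean change, so the paired form is the natural reading, although the article does not state it.

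**Conclusion.** The concern holds in a limited form. The t tests named for the work-performance goal do not account for dyads, the sample size for that goal does, and the cluster-aware route in the same section is not designated as decisive.

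If the tests are run on participant-level paired changes, the false-equivalence rate at the margin is about 5.4% against 5% at the stated ICC, or about 1.44% against 1.25% under four assumed comparisons. That is a small excess in the unsafe direction. It grows only with ICCs that the article does not give.

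It would be wrong to conclude that supervisor ratings are shown to be seriously affected. Shared supervisors are possible under the recruitment text but are not stated, so any figure for them is conditional.

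**What to change.** Name one cluster-respecting equivalence test as primary for work performance. Either of these would do:

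- the mixed-model estimate of mean change with a dyad random effect and small-sample degrees of freedom, with its 1 − 2α confidence interval at the Bonferroni level read against the margin (with four comparisons, α = 0.0125 and a 97.5% interval); or
- a t test on dyad-mean changes.

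In the mixed model the dyad effect must act on the change, through a dyad random effect on change scores or a dyad-by-period effect. A dyad intercept alone cancels from the pre–post contrast and would leave the problem in place. Keep the simple paired t tests as a sensitivity check.

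For supervisor ratings, where one supervisor rates more than one participant, add a supervisor effect on the change in addition to the dyad effect. Replacing the dyad effect would drop the correlation between partners who have different supervisors.

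The cost is a change of wording, since the models are already planned, plus slightly wider intervals and slightly lower power. With the dyad-mean t test, power is about 0.77 at N = 50 and 0.86 at N = 60 under the assumptions that reproduce the stated sample size. Those figures use alpha 0.05; the Bonferroni adjustment lowers power further whichever test is chosen, which is a separate matter.

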**Employee ratings of work performance**				
	1. The World Health Organization Health and Work Performance Questionnaire: Employees rate overall work performance in previous 4 weeks on a 10-point scale; lower employee-rated work performance associated with odds of lower performance in supervisor evaluations and records and experience sampling across multiple job types (odds ratios: 3.2-12.3, *P* values<.05) [55].	X^d^	—^e^	X
	2. Employees rate work quantity, work quality, and interaction quality in previous 4 weeks on a 5-point scale; evidence of face validity [56]; higher work quantity associated with higher physical fitness (*P*=.045), higher work quality associated with higher moderate physical activity (*P*=.002), lower interaction quality associated with greater obesity (*P*=.02) [57].	X	—	X
	3. Work performance by task type: Employees rate ability to perform common work tasks (eg, emails and phone calls) during elliptical use in previous 4 weeks, using a 5-point investigator-generated scale.	—	—	X

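### Holm's procedure would recover some of the power that the Bonferroni correction gives up on the work-performance equivalence tests, at the same familywise error bound

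*Protocol article*

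**What the plan says.** In the protocol article, the section Effects of Desk Pedaling on Work Performance fixes the test: "we will apply the equivalence test of means based on 2 one-sided" t tests, "with the significance level adjusted for multiple comparisons via the Bonferroni correction factor". It mentions no step-down, hierarchical or gatekeeping procedure and does not give the number of comparisons. It also plans a confidence interval approach to equivalence where regression models are used.

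The family can only be inferred. The Design section makes "changes in employee- and supervisor-reported work performance between the 4-week preintervention period and the 4-week intervention period" a primary outcome, which is at least two tests. Table 1 lists an overall rating at both time points and adds: "Employees rate work quantity, work quality, and interaction quality in previous 4 weeks on a 5-point scale". The supervisor gives adapted versions of the same ratings. That makes 4 + 4 = 8 pre-post scores at most. The rating of ability by task type is collected only after the intervention and has no pre-post change.

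The Power and Sample Size section sizes a single test of the change in a total work-performance score: "We also assume an intracluster correlation of 0.05 and a significance level of 0.05", and "a sample size of 50 (25 dyads) gives 80% power to detect equivalence".

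**The concern.** Bonferroni tests every score at 0.05/m, however many of the other scores have already passed. Holm orders the p-values, tests the smallest at 0.05/m, the next at 0.05/(m−1), and so on up to 0.05, and stops at the first failure. Both bound the familywise error at 0.05 under any dependence between scores. Holm needs one p-value per score, and the equivalence test supplies it as the larger of the two one-sided p-values.

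The first aim is to show that performance is unchanged, and it is the only aim for which the article claims power. The error that would defeat it is failing to show equivalence on scores that truly have not changed. Because the sample size was set for one test at 0.05, each loss through the correction comes straight out of the stated 80%.

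**Working it through.** **Inputs from the article:** 50 analysable participants in 25 dyads, margin 0.60 SD, intracluster correlation 0.05, significance level 0.05, two one-sided tests.

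**Assumptions, because the article does not give them:** true change 0; m = 2, 4 or 8 scores; pre-post correlation ρ of 0, 0.3, 0.5 or 0.7; correlation 0.5 between score changes; margin expressed in SDs of a single-occasion score; normal approximation.

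**Standard error of the mean change (in SD units).** The design effect for dyads is 1 + (2 − 1) × 0.05 = 1.05, so SE = √[2(1 − ρ) × 1.05/50].

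**Reproducing the stated power.** For one test at level α, power = 2Φ(0.60/SE − z₁₋α) − 1. With ρ = 0, SE = √0.042 = 0.2049 and 0.60/SE = 2.928. At α = 0.05 this gives 2Φ(2.928 − 1.645) − 1 = 2Φ(1.283) − 1 = 80.05%. The smallest sample size reaching 80% is exactly 50. So ρ = 0 with an undivided 0.05 reproduces the article's figure. With ρ = 0.5 the same formula gives 98.7%.

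**Bonferroni at ρ = 0**, replacing α by 0.05/m:

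- m = 2: 2Φ(2.928 − 1.960) − 1 = 66.7%
- m = 4: 2Φ(2.928 − 2.241) − 1 = 50.7%
- m = 8: 2Φ(2.928 − 2.498) − 1 = 33.3%

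**Holm against Bonferroni.** Holm has no such simple formula, so power was simulated (400,000 replicates). The score p-value is 1 − Φ((0.60 − |estimate|)/SE), and the j-th smallest is compared with 0.05/(m − j + 1). Average power per score, Bonferroni to Holm:

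| Pre-post correlation | 2 scores | 4 scores | 8 scores |
|---|---|---|---|
| 0 | 67% to 75% | 51% to 66% | 33% to 50% |
| 0.3 | 88% to 92% | 79% to 90% | 68% to 85% |
| 0.5 | 97.1% to 98.6% | 94% to 98% | 90% to 97% |
| 0.7 | almost no gain | almost no gain | 99.6% to 100.0% |

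With independent scores the gains are similar. For example, 8 scores at ρ = 0 go from 33% to 47%.

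**What does not change.** The chance that at least one score passes is the same under both procedures, because both test the smallest p-value at 0.05/m. At ρ = 0 with 8 scores it is 90% either way.

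**Error control.** With some or all scores placed at a true change of −0.60 (2 and 8 scores), the highest simulated familywise error under Holm was 0.0498.

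**The case against.** The strongest reply is that nothing here is wrong. Bonferroni is valid and conservative, and changing it protects nobody from a false claim of equivalence. That stands: this is a matter of efficiency.

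The size of the gain also rests on two unstated inputs. The same rater scores the same employee a few weeks apart, so a positive pre-post correlation is plausible, and the gain shrinks as that correlation rises. If the family is only one employee score and one supervisor score, the gain is about 8 to 9 points at correlation 0 and about 1.5 points at 0.5. That also stands, and is why the whole range is shown.

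Three stronger readings are tempting, and the article supports none of them.

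- A reader might point to the chance that all eight scores pass, which goes from 11% to 64% at pre-post correlation 0.3. The article does not make passing every score its success criterion. If it did, no alpha adjustment would be needed.
- A reader might infer that Holm repairs the mismatch between a power calculation at an undivided 0.05 and a test at a divided level. It does not. At correlation 0, average power after the change is still 75%, 66% and 50%. The mismatch is a separate question.
- A reader might call the change free. That is true only of the familywise bound. Realised error moves closer to 0.05, and the matching simultaneous intervals that Bonferroni provides are lost. This matters a little, because intervals are planned for the regression models.

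None of this is a reason to prefer Bonferroni for the test decisions themselves.

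**Conclusion.** A cheap improvement, not an error. On the article's own sample size, margin and intracluster correlation, Holm adds between almost nothing and about 17 points of average power per score. The upper end needs 8 scores and a pre-post correlation of 0 or 0.3. The lower end applies with few scores or a correlation of 0.5 and above. The figures assume no true change, a between-score correlation of 0.5 and the normal approximation. That Holm is never less powerful than Bonferroni at the same familywise bound depends on none of these assumptions.

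**What to change.** In Effects of Desk Pedaling on Work Performance, replace the Bonferroni wording by: Holm step-down procedure applied to the equivalence p-values (the larger of the two one-sided p-values) of the pre-post work-performance scores in Table 1, namely overall rating, work quantity, work quality and interaction quality, each from employee and supervisor. The list matters as much as the method, because that section does not say which scores form the family. If the investigators intend a smaller family, they should list that one instead.

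Report unadjusted 90% confidence intervals for estimation, and state that they are not the multiplicity-adjusted decision rule.

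The cost is a sentence of text and a decision on the family, with no extra participants or data. The downside to disclose is that Holm decisions do not correspond to simple equal-width simultaneous intervals, so an interval may appear to disagree with the test result for a given score.
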